**Table 3 Tab3:**
[figure not shown]
Sample size calculations for the primary comparisons in the study ^1^

^1.^ Needed for each comparison group, based on assumptions of trypanocidal effect explained in the text, including 5% of participant losses

^2.^ Cells with no shade imply feasible scenarios with 60 participants for each group, the recruitment goal for Colombia. *Light grey* cells imply the need to have 60–80 participants per group to make this comparison viable. *Dark grey* cells imply the need to have more than 80 participants per group

### Randomisation

A central, computerised, web-supported application will both assign the study treatment and support remote data collection for every participant. Study personnel at each centre will have their own stock of coded treatments. The system will assign a new treatment upon request at each centre, using random permutations within blocks for predefined strata of age (20–24 years, 25–40 years, 41/older), electrocardiogram status (abnormal /normal) and study centre. That way the randomisation sequence will be concealed for study personnel.

The system will adapt the randomisation scheme to each centre, according to their decision on which treatment groups to include. For Colombian centres, block sizes will be every 5 treatments (one for each study arm). For the rest of the centres (having no masked treatments) the system will assign 2, 3 or 5 different treatments (depending on the inclusion of 2 or 4 active treatment groups, and a control group with deferred treatment). The system will keep the same randomisation strata, but the block sizes will depend on the number of study groups chosen at each centre. In order to ensure concealment of allocation sequence, block sizes will randomly vary at these centres between the number of study groups and its double (i.e. 3 or 6 at a centre having 3 treatment arms).

For Colombian centres, which are offering 120-day-long, masked treatments, the system will allocate two consecutive sequences of 60 days. The groups allocated to active treatment for 60 days (60CD) will have a concealed, randomly allocated period of masked placebo (as treatment for days 1–60 or 61–120) and the remaining days with active medication.

### Data collection and overseeing

Data collected in the study visits and procedures will be entered into a central system, through standard case report forms (CRFs) available to authorised personnel. Most fields in the study CRFs include safeguards (i.e. fields allowing only numbers, a limit of characters or amounts entered). The quality of the information entered will be verified by centralised random validation (10%) and predefined crosschecks between fields of CRFs for each centre. The data will be stored in a secure and transportable system for storage and future analysis.

CRFs for centres outside Colombia may be adapted to local needs, including the visit schedule given by their choice of active treatment or the presence of untreated groups.

### Statistical analysis

Reporting of trial results will include a description of the enrolment process and the most relevant characteristics of the participants. For this purpose we will use counts and proportions or means and standard deviations for discrete and continuous variables, respectively.

Our outcome measures will be discrete variables, with the exemption of mean changes in the BNP levels, a secondary outcome for efficacy. For the purpose of evaluating the efficacy of NFX over placebo, we will test a hypothesis of no difference in the proportions of 1 + PCR at an alpha level of 1%. For the purpose of testing the equivalence of NFX to BZN or between 60CD and 120HD regimes, we will run a one-tailed non-inferiority test at an alpha level of 1%. In order to test for agent-dose interaction for the above comparisons, we will construct logistic regression models with the primary outcome as the event, and the comparison groups and study arms (e.g. NFX 60CD or NFX 120HD) as predictor variables. We will include the interaction dose*agent term in the model and run this test for no differences at an alpha level of 5%.

For the purpose of evaluating mean changes of BNP among groups, we will test for differences using independent-sample Student’s *t* tests comparing the groups of interest (alpha level of 1%). For the dose-agent interaction test (alpha level 5%), we will run an analysis of covariance with the mean changes as response, the comparison and study arms as factors and the interaction term.

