**Fig. 1 Fig1:**
[figure not shown]
Process of treatment allocation

Outside Colombia, because of (1) resource constraints to organise a centralised shipment of study medication or to mask locally their study medication, or (2) local interpretation of the evidence, clinical practice patterns and/or regulations on using trypanocidal treatments, the protocol may have variations in the interventions. EQUITY investigators at those centres will have flexibility to decide on (1) which of the proposed active treatment groups to include and (2) whether or not to have a control group receiving no treatment. Groups receiving active treatment may be any two or all four treatment groups described above. If two groups are chosen, they must use either different agents given at the same dose level and treatment length (either 60CD or 120HD) or the same agent (either NFX or BZN) given at different dose levels and treatment lengths. The choice of including a group not receiving active treatment will depend on the judgement of local investigators or regulatory agencies on whether it is necessary (1) to prove a trypanocidal effect of NFX or (2) to start trypanocidal treatment right upon serology diagnosis.

For centres outside Colombia choosing to include a group receiving no treatment, the allocation ratio will be the same for each active treatment group (i.e. 1:1:1 for those having two active treatment groups and 1:1:1:1:1 for those including all four active treatment groups). In all circumstances, however, all EQUITY centres will use a computerised central randomisation system with a concealed sequence to allocate the local choice of study treatments. All study sites will also have to comply with a blinded process for outcome assessment.

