### Comparisons

EQUITY will test two main efficacy hypotheses, driving the primary comparisons. Firstly, we will test the superiority of NFX, comparing a composite of groups receiving this medication against those allocated to placebo/no treatment (trypanocidal effect of NFX). Secondly, we will test the non-inferiority of (1) a composite of NFX groups compared with those including BZN and (2) 60CD regime groups of any active medication compared with those receiving 120HD regimes. The above comparisons place BZN/60CD as standard treatment, assuming its superiority to placebo. Under this hypothesis, for NFX/120HD to be a valid alternative, we will require its trypanocidal efficacy to be at least two thirds of that for BZN/60CD (see the statistical assumptions made in the “Sample size calculations” section).

Centres outside Colombia may provide data for some, but not all, planned comparisons, depending on their choice of treatment groups. For example, data from centres including only active treatment groups with both NFX and BZN will contribute to test the hypothesis of non-inferiority of NFX to BZN but not to evaluate the trypanocidal efficacy itself. Whatever the choice of treatment groups, however, under our study design our primary comparisons may vary in the number of participants included, but they will only be between randomly allocated treatment groups at a centre level.

We will also test the dose-agent and the treatment-region (southern/northern) interactions for the above comparisons. Data from countries outside Colombia will be included in the applicable comparisons, depending on their treatment groups. We plan to conduct separate sensitivity analyses for our primary comparisons including all randomised participants and those included in Colombia. The safety evaluation will follow the same comparisons described for efficacy.

Secondary comparisons are intended only for efficacy of BZN. They will include (1) testing its superiority over placebo, testing for the treatment-region interaction, and (2) testing the non-inferiority of BZN 120HD compared with BZN 60CD in the overall population. As for the primary comparisons, data from centres outside Colombia may be included, provided they have chosen to randomise their participants to each of these groups.

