A subgroup, exploratory analysis will include (1) age strata at inclusion (20–44/45–65 years), (2) presence/absence of electrocardiographic abnormalities and (3) region of origin (southern/northern South America) for all the planned efficacy comparisons.

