### Sample size calculations

The planned hypotheses in this study will be based on the following assumptions for its sample size:The proportion of participants in the placebo group with at least one positive PCR out of three tests (1 + PCR, the primary outcome for efficacy) will be 75% or higher.As a standard of trypanocidal efficacy, the proportion of (1 + PCR) in the group receiving conventional treatment with BZN (based on results of the BENEFIT trial) will be up to 30% (or 25% in a group receiving BZN in a regime with better tolerance).A treatment with NFX, to be considered non-inferior to BZN, should have at least two thirds of its trypanocidal effect, which is, in terms of the above assumptions, 45% of 1 + PCR (or up to 50% in a group receiving a regime with lower tolerance/efficacy).

Based on the above assumptions, having at least 60–80 participants per study group will allow enough (at least 80%) power to identify a true difference between NFX and placebo or BZN (as negative or positive control for superiority or non-inferiority, respectively), testing a one-tailed hypothesis at an alpha level of 1%. Colombian centres should account for at least 60% of the study population, or 300 participants in the study (60 participants for each group). The overall goal of recruitment, including participants for centres outside Colombia, will be 500, as long as they include at least 80 participants allocated to every study arm (which may vary, depending on the treatment groups chosen at centres outside Colombia). Table 3 shows the scenarios for power calculations for the comparisons on efficacy.

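### The NFX-versus-control test has no centre term, although NFX:control may be 2:1 at some centres and 1:1 at others; it should be stratified by centre

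*Protocol article*

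**What the plan says.** All references are to the protocol article.

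- **Test.** Under Statistical analysis, NFX versus placebo is put as: "we will test a hypothesis of no difference in the proportions of 1 + PCR at an alpha level of 1" per cent. No test statistic, stratification or adjustment is named. The one model given for the primary outcome, the logistic model for the agent-dose interaction, has comparison group, study arm and the interaction as its terms. Centre, age and electrocardiogram status are not among them.
- **Randomisation.** Blocks are formed within "predefined strata of age (20–24 years, 25–40 years, 41/older), electrocardiogram status (abnormal /normal) and study centre" (Randomisation).
- **Allocation.** Colombia has five equal arms, two of them NFX, so NFX:placebo is 2:1 (Interventions). Outside centres may choose two or all four active groups, with or without an untreated control. If they have a control, the ratio is "1:1:1 for those having two active treatment groups and 1:1:1:1:1 for those including all four active treatment groups" (Interventions, text after Fig. 1).
- **Who is compared.** The Comparisons section pools all NFX groups against all placebo or untreated participants. It says of the primary comparisons that "they will only be between randomly allocated treatment groups at a centre level". It also plans a Colombia-only sensitivity analysis and a treatment-region interaction test.

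**The concern.** Pooling centres with different allocation ratios breaks the balance that randomisation gives within each centre. If one centre supplies two NFX participants per control and another supplies one, the pooled NFX and control groups have a different mix of centres. Any difference between centres in the chance of a positive PCR then enters the estimated NFX effect, and the 1% error rate is no longer guaranteed. The comparison at risk is the one meant to establish that NFX has a trypanocidal effect. The secondary comparison of BZN with placebo has the same structure.

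The eventual mix of ratios was not settled when the article was written: recruitment outside Colombia was open and further centres were being sought (Trial status).

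**Working it through.** **1. The plan's own sample size.** Inputs from Sample size calculations: control positivity "will be 75% or higher"; NFX 45%, or up to 50%; "having at least 60–80 participants per study group will allow enough (at least 80%) power"; "testing a one-tailed hypothesis at an alpha level of 1" per cent; 5% losses (Table 3 footnote). Formula per group, with p̄ the mean of p₁ and p₂:

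n = [z₀.₉₉ √(2p̄(1−p̄)) + z₀.₈₀ √(p₁(1−p₁) + p₂(1−p₂))]² / (p₁−p₂)²

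- 75% v 45%: (1.612 + 0.555)² / 0.09 = 52.2, so 53; 53/0.95 gives 56.
- 75% v 50%: (1.593 + 0.557)² / 0.0625 = 73.9, so 74; 74/0.95 gives 78.

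The stated 60–80 per group is reproduced for these scenarios. The calculation treats the comparison as two simple proportions.

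**2. NFX:control ratio by permitted design.**

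| Centre | NFX:control |
|---|---|
| Colombia, or outside with five arms | 2:1 |
| Two NFX arms + control | 2:1 |
| One NFX arm + one BZN arm + control | 1:1 |
| No control, or no NFX arm | does not contribute |

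**3. Bias of a pooled difference when NFX has no effect.**

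Bias = (outside share of controls − outside share of NFX) × (outside positivity − Colombian positivity)

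Upper-end case: Colombia 120 NFX and 60 placebo (300 participants, 60 per arm). The other 200 of the 500 are all in 1:1:1 centres with one NFX arm, one BZN arm and a control, so about 67 NFX and 67 controls. This can still meet the 80-per-arm rule: with half of the 200 in 60CD centres and half in 120HD centres, each active arm has about 60 + 33 = 93.

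- Outside share of controls: 67/127 = 0.528.
- Outside share of NFX: 67/187 = 0.358.
- Difference: 0.169, so each 10 points of difference in positivity gives 1.7 points of bias.

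**4. Type I error.** Simulated trials (at least 400,000 per scenario), no NFX effect, Colombian positivity 75%. Outside positivity is an assumption, varied over a range. The pooled z-test and the centre-stratified Mantel-Haenszel test are both one-sided at a nominal 1%.

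| Outside positivity | Bias towards NFX (points) | Pooled test | Stratified test |
|---|---|---|---|
| 75% | 0 | 1.0% | 1.0% |
| 85% | +1.7 | 2.2% | 0.9% |
| 95% | +3.4 | 5.1% | 0.9% |
| 65% | −1.7 | 0.4% | 1.0% |
| 55% | −3.4 | 0.1% | 1.0% |

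If the test is read as two-sided at 1%, the pooled error for 85% and 95% is 1.3% and 3.0%.

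**5. Less extreme mixes.**

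- Half of the outside participants in five-arm centres (40:20) and half in 1:1:1 centres (33:33), outside positivity 85% or 95%: bias 0.9 or 1.8 points, pooled error 1.4% or about 2.0%.
- All contributing centres 2:1 (120:60 plus 80:40): bias 0, pooled error 0.7–0.9%, slightly conservative.

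**6. A true 25-point effect, outside positivity 20 points lower** (Colombia 75% v 50%, outside 55% v 30%; 120:60 plus 67:67). The pooled estimate averages 21.6 points instead of 25, and power is 93.3% pooled against 98.3% stratified.

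**7. The other primary comparisons.** NFX v BZN is 1:1 in every centre with both agents, and 60CD v 120HD is 1:1 in every centre with both regimes. The centre mix is therefore the same on both sides, and pooling gives no bias of this kind.

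**The case against.** The strongest reply is that the protocol never says the test is crude or pooled. A Mantel-Haenszel test also tests for no difference in proportions, and a condensed article may leave the statistic to an analysis plan. This stands in part: the unstratified analysis is a reading of the text, not a quotation. But the section does name other tests (independent-sample t tests for BNP) and does list the predictors of its logistic model, and centre is in none of them. The sample size also uses simple proportions.

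Second, the Comparisons section says that "they will only be between randomly allocated treatment groups at a centre level". This removes the worst source of bias, centres with NFX but no control. It settles which centres enter a comparison, however, not how their results are combined. Once 2:1 and 1:1 centres both qualify, the problem in the working remains.

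Third, the planned Colombia-only analysis is 2:1 throughout and free of this bias. With 114 v 57 evaluable (5% losses), its power is about 81% for 75% v 50% and 94% for 75% v 45%. That is a real safeguard, but it is a sensitivity analysis and not the primary test.

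Some stronger readings are tempting, and the document does not support them:

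- *That NFX versus control is confounded.* It can be. It is only if 1:1 centres join and their underlying positivity differs. A control group outside Colombia is optional.
- *That the protocol expects such a difference.* The Background reports geographical variation in response to BZN, not in untreated positivity, and the sample size assumes one placebo rate.
- *That the non-inferiority comparisons are biased too.* They are 1:1 in every eligible centre.
- *That ignoring the strata inflates the error by itself.* With equal ratios it makes the test slightly conservative.
- *That the age-subgroup cut at 45 is an error because randomisation cuts at 41.* The subgroup is labelled exploratory and need not follow the strata.

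**Conclusion.** The point holds in a conditional form. The protocol permits NFX:control ratios of 2:1 and 1:1 within one comparison and states a test with no centre term, so the comparison can be confounded by centre.

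In the upper-end mix, from a Colombian positivity of 75%, outside positivity 10 to 20 points higher raises the one-sided type I error from 1% to about 2.2% to 5%. Lower outside positivity makes the test conservative and understates the NFX effect. With half of the outside participants in 1:1:1 centres the error is about 1.4% to 2.0%, and with all centres at 2:1 there is no bias. The regional differences and the centre mix are assumptions, because the document gives neither. Stratifying by centre held the error at 0.9–1.0% in every scenario shown.

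This should be fixed. Because the bias is conditional and a bias-free Colombia-only analysis is planned, the documents do not support treating it as a certain defect of the trial.

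**What to change.** State that the primary NFX-versus-control comparison and the secondary BZN-versus-placebo comparison are stratified by centre. Suitable methods are a Mantel-Haenszel risk difference, or a logistic model with centre from which a standardised risk difference is derived. Include the age and electrocardiogram strata, and give a rule set in advance for collapsing sparse strata. Add the same terms to the interaction models.

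Use the same stratification for NFX versus BZN and for 60CD versus 120HD. There it serves correct standard errors and precision only, not the removal of bias.

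The cost is a few sentences of analysis wording, settled before unblinding. Participant numbers, arms, visits and data collection are unchanged. The exploratory age subgroup can stay as it is.

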**Methods:**

The goal of this randomised, concealed, blind, parallel-group trial is to inform the trypanocidal efficacy and safety of NFX and its equivalence to BZN among individuals with *T. cruzi* positive serology (TC+). Eligible individuals are TC+, 20–65 years old, with no apparent symptoms/signs or uncontrolled risk factors for cardiomyopathy and at negligible risk of re-infection. Consenting individuals (adherent to a 10-day placebo run-in phase) receive a 120-day BID blinded treatment with NFX, BZN or matching placebo (2:2:1 ratio). The four active medication arms include (1) a randomly allocated sequence of 60-day, conventional-dose (60CD) regimes (BZN 300 mg/day or NFX 480 mg/day, ratio 1:1), followed or preceded by a 60-day placebo treatment, or (2) 120-day half-dose (120HD) regimes (BZN 150 mg/day or NFX 240 mg/day, ratio 1:1). The primary efficacy outcome is the proportion of participants testing positive at least once for up to three polymerase chain reaction (PCR) assays (1 + PCR) 12–18 months after randomisation. A composite safety outcome includes moderate to severe adverse reactions, consistent blood marker abnormalities or treatment abandons. The trial outside Colombia (expected to recruit at least 60% of participants) is pragmatic; it may be open-label and not include all treatment groups, but it must adhere to the randomisation and data administration system and guarantee a blinded efficacy outcome evaluation. Our main comparisons include NFX groups with placebo (for superiority), NFX versus BZN groups and 60CD versus 120HD groups (for non-inferiority) and testing for the agent-dose and group-region interactions. Assuming a 1 + PCR ≥ 75% in the placebo group, up to 25% among BZN-treated and an absolute difference of up to ≥ 25% with NFX to claim its trypanocidal effect, 60–80 participants per group (at least 300 from Colombia) are needed to test our hypotheses (80–90% power; one-sided alpha level 1%).

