**Discussion:**

The EQUITY trial will inform the trypanocidal effect and equivalence of nitroderivative agents NFX and BZN, particularly outside southern cone countries. Its results may challenge current recommendations and inform choices for these agents.

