### Study design

We will conduct a randomised, concealed, multi-centre, parallel-group, blind trial, testing the superiority of NFX over placebo and its non-inferiority compared with BZN.

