EQUITY will provide data and insight on three important aspects regarding the use of the two recognised possibilities for trypanocidal therapy, BZN and NFX. While testing the efficacy of NFX as a trypanocidal agent and the equivalence of these two agents, this trial will also test two different treatment regimes. The process to establish the daily dose and length of treatment for BZN and NFX (two agents developed since the 1960s) did not undergo rigorous evaluation. Recent reports on pharmacokinetics of BZN in children have suggested that under the recommended daily dose for adults (5 mg/kg a day) blood levels would exceed by twofold those with a proven trypanocidal effect for children [21]. If that is the case, and side effects are dose-related, halving the dose may promote tolerance. Conversely, another study in adults has suggested that serum levels of BZN are not associated with side effects [22]. Other authors have suggested that the length of exposure (i.e. cumulative doses) is what may trigger intolerance to BZN [23]. Others have, in fact, started tests of shorter, intermittent treatments with BZN [24]. Guidelines for treatment of *T. cruzi* infection indeed vary in the dose, but also in the length of therapy, mainly between 60 and 90 days [25]. Through comparison of the 60CD and 120HD treatment schemes, our study will inform whether tolerance to nitro derivatives NFX or BZN treatment is associated with doses or exposure.

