EQUITY has some limitations. Firstly, its primary efficacy outcome is parasite-related. Establishing an effective regime that is well tolerated is an intermediate, necessary step for future testing of its clinical impact. In fact, in the placebo-controlled BENEFIT trial (where 20% of the population did not respond to BZN and 13% abandoned their treatment), the clinical impact went consistently towards benefit, but without statistically significant effect (7% reduction in its primary outcome, a composite of cardiac complications or death) [11]. Thus, choice of a treatment scheme with a better efficacy/tolerance ratio would be critical to identify a potential clinical impact. Secondly, as the trial relies on limited resources, it will have a limited geographical variety in its population. By having Colombia as the main participating country, we will address two needs: to run a new trial testing NFX (the first in Colombia, where a previous quasi-experiment showed positive results [26]), and to replicate (or challenge) previous results of the BENEFIT trial showing no trypanocidal effect. Thirdly, our study will test a limited amount of possibilities for trypanocidal therapy. The EQUITY trial will focus on the foundations to use NFX and to recommend it as an equivalent of BZN. Keeping the trial within this reach allows statistical power for the two main questions, at a cost of leaving, for example, combinations, other treatment schemes and other agents untested.

Finally, conducting a trial like EQUITY will, for the local capacity, provide a useful and constructive experience. This trial will increase much-needed clinical trial data on *T. cruzi*-infected populations from Andean countries. In that regard, EQUITY will join two recent trials including Bolivian patients or immigrants living in Spain [12, 13]. Investigator-initiated trials originating from Colombia are still scarce, and are a challenge for promotion among funding and regulatory agencies as well as research departments and laboratories. For this and other neglected tropical diseases, this type of trials may also be seen as a responsibility for endemic countries.

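### The one-tailed non-inferiority test is labelled a test of equivalence; a pass can support non-inferior but not equivalent

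*Protocol article*

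**What the plan says.** The protocol article uses two vocabularies for one comparison.

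**Non-inferiority**, wherever the comparison is specified:
- Study design: "testing the superiority of NFX over placebo and its non-inferiority compared with BZN".
- Comparisons: "Secondly, we will test the non-inferiority of (1) a composite of NFX groups compared with those including BZN". The regimen contrast (60CD and 120HD) is treated the same way. The requirement is at least two thirds of the standard's trypanocidal efficacy.
- Sample size calculations: "testing a one-tailed hypothesis at an alpha level of 1" per cent. The limit for NFX is 45% positive PCR (up to 50% for a less tolerated or less effective regimen), against 30% (or 25%) on BZN.
- The abstract's list of main comparisons also names non-inferiority for both contrasts.

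**Equivalence**, for the purpose of the test and the use of the result:
- Statistical analysis: "For the purpose of testing the equivalence of NFX to BZN or between 60CD and 120HD regimes, we will run a one-tailed non-inferiority test".
- Abstract, Methods: the goal "is to inform the trypanocidal efficacy and safety of NFX and its equivalence to BZN".
- Abstract, Discussion: "The EQUITY trial will inform the trypanocidal effect and equivalence of nitroderivative agents NFX and BZN".
- Discussion: "While testing the efficacy of NFX as a trypanocidal agent and the equivalence of these two agents", and later "The EQUITY trial will focus on the foundations to use NFX and to recommend it as an equivalent of BZN".

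No limit, test or interval rule is given for the direction in which BZN does worse than NFX.

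**The concern.** Equivalence means that the difference is bounded on both sides. A one-tailed non-inferiority test bounds one side, here the side where NFX is worse. A pass is compatible with NFX being similar to BZN and also with NFX being far better.

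The unbounded side matters here. The Background reports that an earlier placebo-controlled trial found BZN trypanocidal in Argentina and Brazil but not in participants from Colombia and El Salvador. The Discussion places Colombia among the countries that lack data or where BZN appears not to work, and lists replicating or challenging that result as one of the needs addressed. Colombian centres are to supply at least 60% of participants. If NFX works there and BZN does little, the non-inferiority test will pass. Reporting that pass under the label used in the Statistical analysis section would favour treating the drugs as interchangeable when the data show that they are not.

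**Working it through.** **Inputs from the protocol.** One-sided alpha 1% (z = 2.326); 60–80 participants per arm; 5% losses (Table 3 footnote); two arms per agent, pooled. Evaluable per agent: 2 × 60 × 0.95 = 114, or 2 × 80 × 0.95 = 152. Margin: 45% − 30% = 15 points; the looser limit of 50% gives 20 to 25 points. Placebo rate: 75%.

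**Assumptions of this check.** The lower margin mirrors the upper one, because the protocol gives none. The normal approximation is used with unpooled standard error. The true rates in the scenarios are illustrative. Table 3 is not shown, so its cells were not checked; the argument does not need them.

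**Step 1: the plan's own figure.** With 80% power and 5% losses, NFX 50% against placebo 75% needs 74, or 78 after losses; NFX 45% against 75% needs 56 after losses. Non-inferiority with a 25-point margin needs 65 (both rates 25%) or 72 (both 30%) per comparison group. The stated 60–80 is therefore reproduced under a superiority and non-inferiority reading. With a 15-point margin and both rates 30%, non-inferiority needs 198 per comparison group.

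**Step 2: chance of a pass when BZN is the worse drug.** Let d = p(NFX) − p(BZN), m = margin, and SE = √[p(NFX)(1 − p(NFX))/n + p(BZN)(1 − p(BZN))/n].

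- P(non-inferiority) = Φ((m − d)/SE − 2.326)
- P(both sides bounded) = Φ((m − d)/SE − 2.326) − Φ((−m − d)/SE + 2.326)

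NFX 30%, BZN 45%, n = 114, m = 0.15:
- SE = √[(0.21 + 0.2475)/114] = 0.0634
- P(non-inferiority) = Φ(0.30/0.0634 − 2.326) = Φ(2.41) = 0.992
- P(both sides bounded) = 0.992 − Φ(0 + 2.326) = 0.992 − 0.990 = 0.002

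| NFX | BZN | n per agent | Margin (points) | Planned test passes | Two-sided rule passes |
|---|---|---|---|---|---|
| 30% | 45% | 114 | 15 | 99.2% | 0.2% |
| 30% | 45% | 152 | 15 | 99.9% | 0.9% |
| 25% | 50% | 114 | 15 to 25 | about 100% | at most 1% |
| 45% | 75% (placebo rate) | 114 | 15 to 25 | about 100% | under 0.1% |

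Simulation with 120 per agent agrees. For NFX 25% and BZN 50% at 15 points, the planned test passed in 99.999% of draws; for 25% and 75% it passed in essentially all.

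**Step 3: what a formal equivalence claim would cost.** Both rates 30%, n = 114, m = 0.15: SE = √(0.42/114) = 0.0607. The 98% interval has half-width 2.326 × 0.0607 = 0.141. It fits inside ±15 points only if the observed difference is within about 0.9 points of zero.

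| Margin (points) | Equivalence shown, 114 per agent | Equivalence shown, 152 per agent |
|---|---|---|
| ±15 | 12% | 40% |
| ±20 | 67% | 86% |
| ±25 | 93% | 98% |

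At ±15 points, 80% power for equivalence would need 256 per comparison group including losses.

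**The case against.** The strongest reply is that this is a matter of label. Every section that specifies the comparison says non-inferiority, and the disputed sentence itself names a one-tailed non-inferiority test. That stands. A reader might infer that hypothesis, tail and alpha conflict across the article. They do not, and no section describes a two-sided equivalence test.

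A reader might also infer that the trial is committed to declaring the drugs equivalent even when BZN is far worse. The documents do not say so. The abstract and the Discussion state aims, and no passage says a pass will be reported as equivalence. The one stated criterion, in Comparisons, is one-directional: whether the alternative retains enough efficacy to be used. Even the phrase about recommending NFX could mean only that NFX may stand in for BZN.

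The plan also includes a secondary BZN–placebo test with a region interaction, which could expose an ineffective BZN, and the authors foresee results that challenge interchangeability. This lowers the practical risk, but it does not change what a pass on the primary comparison is called.

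Two further replies are fair. Any non-inferiority test passes when the new drug is much better, so Step 2 shows no defect in the test, only the gap between test and label. And nothing in the protocol suggests that either 60CD or 120HD is expected to be far worse, so for the regimens the mislabelling is the same but the reason for particular worry is absent.

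Finally, interval reporting may well sit in an analysis plan that is not shown. The point rests on the article's own sentence, which fixes both a purpose and a test that cannot serve it.

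**Conclusion.** The concern holds as a mismatch between the test and the conclusion it is said to serve. The planned test supports non-inferior and nothing stronger. If BZN has little effect in Colombia and NFX works, the test passes almost surely although the drugs differ greatly: 99% at NFX 30% and BZN 45% with 114 per agent and a 15-point margin, against under 1% for a two-sided rule. The first figure depends on the assumed rates and margin; the second depends also on the assumed symmetric lower margin. The test, its alpha and the sample size are not shown to be wrong by this point. Because the correction decides what the trial may claim about two drugs now recommended as alternatives, it is more than clerical.

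**What to change.** 1. In the Statistical analysis section, replace *testing the equivalence* with *testing the non-inferiority*, for the agents and for the regimens, and limit the primary conclusion to non-inferior.
2. Report the two-sided 98% confidence interval for the NFX–BZN difference and for the regimen difference. It matches a one-sided 1% test on each side.
3. Allow the word equivalent only if both interval limits lie within a margin prespecified on each side. Align the abstract and Discussion with this rule.

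The cost is wording and one interval per contrast, with no extra participants. The price is a more modest claim: at 15 points and true rates of 30%, formal equivalence would be shown in about 12% (60 per arm) to 40% (80 per arm) of trials, so most positive results would be worded as non-inferiority. Wider margins would make the claim easier to reach (Step 3), but the margin must be justified in advance and not chosen for that reason.
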